## Abstract

**Background:**

Interventions to better manage aggressive behaviour and reduce recidivism are a primary concern for corrective services. Nutritional interventions to correct prisoner behaviour have been largely overlooked in the literature. Emerging evidence suggests that dietary intake influences aggressive behaviours and that nutritional supplementation with omega-3 long chain polyunsaturated fatty acids (n-3 LCPUFA) could attenuate both the severity and frequency of aggressive behaviour.

**Methods:**

Adult male prisoners who have a history of aggressive behaviour (*n* = 600) will be recruited from at least 6 Correctional Centres and randomised to receive either n-3 LCPUFA or placebo supplementation for a 16-week duration. Treatment will be with either 1 g/day of n-3 LCPUFA (694 mg DHA and 397 mg EPA) or placebo capsules, which are a corn/soy oil blend and are identical in size and colour.

The primary outcome measure is the Inmate Behavioural Observation Scale (IBOS): an objective measure of aggressive behaviour. Secondary outcome measures include questionnaires (including aggression, attention deficit disorder, impulsivity, depression/anxiety/stress scales), engagement in programmes, recidivism and quality of life. Baseline and post-intervention assessments include the IBOS, questionnaires and blood to measure the levels of n-3 LCPUFA.

**Discussion:**

To conclusively test the potential that increasing n-3 LCPUFA intakes can improve rates of prisoner aggression and associated mental health and violence-related social system management costs, we propose an adequately powered multi-centre, double-blind, randomised controlled trial, examining the effects of n-3 LCPUFA supplementation on aggressive behaviour in adult male prisoners. If successful, this study will inform prisoner policy with respect to nutrition and by inference contribute to a broader community approach to preventative mental health practices.

**Trial registration:**

Australian New Zealand Clinical Trial Registry (ANZCTR) ACTRN12618001665224. Registered on 10 October 2018.

## Introduction

### Background and rationale {6a}

While the importance of good nutrition for optimal mental health is increasingly being recognised [1], poor nutrition and low educational attainment are more common in low socio-economic groups and both are defining characteristics of prisoner populations. A vast body of literature has attested to the benefits of dietary supplementation on mental health issues in general [1] and an emerging literature suggests that dietary supplementation may also impact upon aggressive behaviour [2, 3]. Nutrition is rarely supplemented as a strategy for improving prison behavioural outcomes, even as part of existing mental health intervention programmes which tend to focus on acute needs rather than long-term management [4]. Given substantial societal costs associated with violence and the potential for violence prevention with a simple, accessible and low-cost dietary modification among those at elevated risk of these behaviours, rigorous studies to establish an evidence base are required. The proposed study is designed to contribute to that broad endeavour.

#### Why n-3 LCPUFA?

Omega-3 long chain polyunsaturated fatty acids (n-3 LCPUFA) have cardiovascular health benefits [5, 6], and there is emerging evidence for n-3 LCPUFA benefits for mental health benefit, including reducing violent or aggressive behaviour [7].

n-3 LCPUFA were discovered in the 1970s when researchers set out to investigate why Inuit people of Greenland had high consumption of fat via whale, seal and fish yet low incidence of cardiovascular disease (CVD) [8]. Their findings were extended to other populations that had high fish consumption and low CVD incidence [9, 10], and n-3 LCPUFA have since been associated with numerous health benefits. However, it is well established that n-3 LCPUFA are specifically and substantially deficient in Australian (‘Western’) diets [11, 12]. This is due to relatively low consumption of fish/seafood, the richest sources of n-3 LCPUFA, in particular the semi-essential eicosapentaenoic acid (EPA) and docosahexaenoic acid (DHA). The development of an ‘omega-3 index’ (erythrocyte EPA + DHA levels as percent of total fatty acids) [13], pooling results from numerous trials in cardiac disease, showed that an index ≤4% was associated with the greatest risk for cardiac mortality while ≥8% conferred the greatest protection. In Australia, the average index is 5% [14, 15].

#### Addressing the n-3 LCPUFA controversy

Randomised controlled trials and meta-analysis of trials up to 2002 demonstrated that supplementation with n-3 LCPUFA resulted in up to 45% reduction in overall mortality from cardiac death [5, 16]. However, reviews and meta-analyses of more recent trials reported a lack of efficacy, questioning whether increased n-3 LCPUFA levels improve health outcomes [17, 18]. Nevertheless, critical analyses of these recent trials have suggested that their observed lack of efficacy may have been due to methodological problems arising across populations studied [19]. Following the earlier successful trials, the American Heart Association issued guidelines for people with heart disease, suggesting consumption of at least 2 fish meals per week [20] in addition to fish oil supplements [21]. Between 2000 and 2010, the importation of fish oils into the USA escalated more than 10-fold from 2000 to 22,000 metric tonnes [22]. However, trials conducted after 2002 failed to screen people for high fish and/or fish oil supplement intake resulting in great variability of n-3 LCPUFA status across trial conditions [19]. Where screening did occur, the upper 50% of the control subjects and the lower 50% of the fish oil intervention subjects overlapped [23], suggesting that the 2 groups were not separated enough in use of fish oils to demonstrate an effect in the test arm (n-3 LCPUFA). Thus, robust trials of using fish oil to address omega-3 deficiency need to attenuate possible ceiling effects created by high baseline levels, by taking blood samples to determine compliance and correlations between increased omega-3 index and response. This is supported by the International Society for the Study of Fatty Acids and Lipids (ISSFAL) recent position statement, which highlights the importance of measuring blood n-3 LCPUFA levels in research [24].

#### n-3 LCPUFA and mental health

Both EPA and DHA are important for optimal brain function and have different mechanisms of action [25]. DHA is a structural component of neurons, affecting both physicochemical properties of the neuronal membrane (such as membrane fluidity and permeability) but also neurotransmission through gene expression modulation, neuronal enzyme activity and postsynaptic receptors [26, 27]. Due to its involvement in the regulation of the central neurotransmission such as dopamine and serotonin, DHA along with EPA administration seems beneficial in reducing depressive symptoms [28]. EPA is not concentrated in neural cell membranes but it may have neuro-immunological and vascular effects [25, 29]. EPA competes with the omega-6 arachidonic acid for the production of eicosanoids, and the EPA-derived eicosanoids have anti-inflammatory, anti-thrombogenic and vasodilatory effects resulting in increased blood flow in the brain and improved neuroprotection [25, 29]. It is well established that DHA plays an important role in neurological development and suboptimal levels are associated with mental health issues such as hyperactivity, poor impulse control and depression [7] and low omega-3 index (an average of 4.1% [30] and an average of 3.0% in people at ultra-high risk of psychosis [31]) is associated with increased mental illness [30, 32]. Therefore, a body of research has investigated the role of n-3 LCPUFA acids in mental health [2, 25, 33].

#### n-3 LCPUFA, aggression and violent behaviour

n-3 LCPUFA may be important in controlling aggression/hostility and self-harm [32, 34, 35]. Significant decreases in anger and anxiety in a population of substance abusers were reported after supplementation of EPA and DHA for 3 months [36]. EPA has also been shown to reduce antisocial and aggressive behaviours [37]. Eleven out of 14 randomised controlled trial studies reported a positive effect of fish oils on aggression/hostility [35].

#### Inmate Behaviour Observation Scale (IBOS)

The IBOS was developed by ([name], [name], [name]. The Inmate Behaviour Observation Scale (IBOS): A measure of prisoner aggression and violence based on inmate case notes, in preparation/forthcoming) and is an observation-based measure of aggressive behaviour based on inmate case notes. The IBOS was developed to overcome the different environments across different Correctional Centres, and it has been shown to have construct validity and inter-rater reliability. The IBOS is an ideal tool to use in multi-centre trials.

#### Prisoner populations, mental health and violence

The logistics of conducting intervention trials in corrective services settings are challenging, and hence, only two supplementation studies [2, 3] have been published to date in Europe in adult male prisoners. Both of these well-controlled studies showed that, with nutritional supplementation of multivitamins/minerals and n-3 LCPUFA, there was a 26–35% reduction in the number and severity of in-prison reprimands, particularly for violent behaviour [2, 3]. However, both of these studies had two significant limitations. First, neither of these studies acquired blood samples to measure the changes in n-3 LCPUFA and hence these studies were unable to correlate the changes in blood n-3 LCPUFA levels with reduced aggressive behaviour. We collected blood samples in our recent feasibility study and will address this limitation in the proposed multi-centre trial. Second, the measure of aggression used within the two previous studies, in-prison reprimands, is influenced by variability both within and between institutions with respect to rules and tolerance ([name], [name], [name]. The Inmate Behaviour Observation Scale (IBOS): A measure of prisoner aggression and violence based on inmate case notes, in preparation/forthcoming). In this study, we used the IBOS, which more specifically targets aggressive behaviour and is less susceptible to institutional variation ([name], [name], [name]. The Inmate Behaviour Observation Scale (IBOS): A measure of prisoner aggression and violence based on inmate case notes, in preparation/forthcoming).

We conducted a feasibility/pilot study at the South Coast Correctional Centre (SCCC) in Nowra, NSW, in 2013 in adult male prisoners [38]. The sample was restricted to male prisoners for both pragmatic and scientific reasons. With regard to the former, the number of female inmates is greatly fewer than male inmates. As such, the task of recruiting a sufficient sample of female offenders for both the purposes of within-group and between-group comparisons was deemed to be difficult to achieve. More importantly perhaps, the literature suggests that female prisoners tend to internalise their anger [39] and that the primary antecedents of female offending are predominantly environmental challenges [40]. In addition to this, there is evidence that the metabolism and bioavailability of omega-3 fatty acids differ between males and females, a variable that would influence the interpretation of results [41–43].

Baseline data showed negative correlations between blood n-3 LCPUFA levels and measures of aggressive behaviour [7]. We have shown that conducting a supplementation trial in a Correctional Centre is feasible [38] and the study design for the multi-centre trial is based on these recommendations [38]: (1) to collaborate with, and receive support from the Department of Correctional Services; (2) the need to provide incentives to prisoners to aid in recruitment; (3) having an external pathology provider take the blood samples; (4) a designated Correctional Officer as a Project Officer to ensure compliance; (5) the need to restrict buy-ups of cans of tuna and n-3 LCPUFA supplements to reduce potential confoundings; (6) the Correctional Officers require training on how to score the IBOS and how to complete the questionnaires; and (7) the inclusion and exclusion criteria need to ensure that participants are likely to remain in the study for the study duration, are aggressive at baseline (IBOS of 1 or greater) and have an omega-3 index below 6% [38].

## Objectives {7}

### Aims

#### Primary aim

To determine if n-3 LCPUFA supplementation reduces aggressive behaviour in adult male offenders in the Correctional Centres using a randomised, double-blind, placebo-controlled intervention and translate these outcomes into policy and practice.

#### Secondary aims

To estimate the impacts of n-3 LCPUFA supplementation on attention deficit disorder behaviour, depression and anxiety, impulsiveness, engagement in and outcomes of rehabilitation programmes, recidivism and physical health (quality of life and muscle strength).

### Hypothesis

#### Primary hypothesis

We hypothesise that 16 weeks of n-3 LCPUFA supplementation will result in significant reductions in aggressive behaviour compared to placebo alone.

#### Secondary hypotheses

We also hypothesise that 16 weeks of n-3 LCPUFA supplementation will result in significant reductions in institutional reprimands and improvements in attention deficit disorder behaviour, depression and anxiety, impulsiveness, engagement in and outcomes of rehabilitation programmes, recidivism and physical health (quality of life and muscle strength).

The null hypothesis is that there will be no difference between the treatments and controls.

## Trial design {8}

The study design is a multi-centre, double-blind, superiority, randomised controlled trial with a 1:1 allocation between experimental and placebo groups.

## Methods: participants, interventions and outcomes

### Study setting

The study will take place in New South Wales and South Australia in Australia in at least 6 Correctional Centres. The Correctional Centres contain between 400 and 1000 prisoners including minimum, medium and maximum security. List of study sites can be obtained in the trial registration (http://www.anzctr.org.au/trialSearch.aspx) and enter ACTRN12618001665224.

#### Public title

The public title of this trial is ‘Does omega-3 supplementation reduce aggressive behaviour in adult male prisoners?’

#### Summary results

Summary results will be listed on the ANZCTR databases once published.

#### Individual clinical trial participant-level data (IPD) sharing statement

The study authors plan to share de-identified IPD underlying published results. Data will be available after all researchers involved in this trial have finished analysing and publishing the data. The de-identified data will be available following the last publication from our research group. No end date is yet determined. Data will be available on request from the study’s CIA BJM (lead and corresponding author) on a case-by-case basis.

All items from the WHO Trial Registration Data Set are available on the ANZCTR databases and within this manuscript.

Based on our successful model from the feasibility study [38], one Correctional Centre Officer per site will be seconded to the research project and they will take on the role of trial coordinator, referred to as Project Officers. Project Officers will be trained at the University of Wollongong prior to the commencement of the trial. Project Officers will determine the 8-week baseline IBOS to identify those prisoners with IBOS scores of greater than 0 and invite them to participate in the intervention trial.

### Eligibility criteria {10}

The participants are adult (aged 18 years or older), male prisoners residing in Correctional Centres.

Figure 1 shows the flow diagram for screening, eligibility and randomisation. Inclusion criteria are male prisoners with a baseline IBOS score of greater than 0 and erythrocyte omega-3 index less than 6% of total erythrocyte fatty acids. The IBOS score is explained below.

**Fig. 1 Fig1:**
[figure not shown]
CONSORT 2010 flow diagram

Exclusion criteria include (1) those prisoners due to leave prison within 16 weeks, (2) prisoners with a baseline IBOS equal to or less than 0, (3) prisoners on blood thinning agents and/or not medically fit and (4) prisoners with an erythrocyte omega-3 index of greater than 6% of total erythrocyte fatty acids.

### Who will take informed consent? {26a}

A potential participant is approached for enrolment in the study if they meet (i) the release date (i.e. will be in the Correctional Centre for the duration of the study) and (ii) the baseline IBOS score (i.e. a score of 1 or greater, indicating aggressive behaviour). The Project Officer will approach these prisoners for enrolment into the study and will take written informed consent. Consent will be sought using scripts incorporating teach-back techniques to ensure participants understand the process. These scripts were developed in consultation with Correctional Officers and a communications specialist to ensure clarity and accuracy. For example, the script regarding consent for the Project Officers to access medical records is ‘The first step is that we need to check your medical records, as there might be a risk involved if you are on medications that thins your blood. You might have to be excluded from the study at this point. We have to ensure all participants are medically approved to take part’ with the teach-back question of ‘Can you tell me why we need to check your medical record?’ Participants will be given up to a week to consider consenting to the study.

### Additional consent provisions for collection and use of participant data and biological specimens {26b}

Additional consent will be sought from the study participants in terms of the storage of their blood samples (bio-banking) and collection of blood samples for future genetic analysis. The study participants will receive separate participant information sheets and consent forms, and the Project Officer will obtain written informed consent using scripts and the teach-back method. Future research may be conducted using these stored blood samples after obtaining the necessary ethics approval.

## Interventions

### Explanation for the choice of comparators {6b}

The algal DHA-O capsules are ~ 1 g with 509.2 mg/capsule DHA/EPA (i.e. DHA 324 mg/capsule and EPA 185.3 mg/capsule), hence providing a daily dose of 1091 mg omega-3 (694 mg DHA and 397 mg EPA). No intervention has assessed blood levels of omega-3; hence, the use of a placebo is permitted [44]. The placebo capsules are a corn/soy oil blend and are identical in size and colour to the active capsules.

### Intervention description {11a}

The Correctional Officer on secondment as the Project Officer will deliver the supplements to the enrolled prisoners on Mondays, Wednesdays and Fridays, and they will watch participants swallow the supplements to ensure compliance. Supplements will be provided over a 16-week duration, the average supplement duration of the 2 previous studies [2, 3]. Baseline and post-intervention measures include IBOS, institutional records of reprimands or misconduct, questionnaires and measure of muscle strength, and blood samples to measure the erythrocyte omega-3 index levels will also be used as a measure of compliance. The questionnaires are demographic (in house), Aggression Questionnaire (AQ) [45]; Browns Attention Deficit Disorder Scales (BADDS) [46]; Conners’ Attention Deficit Hyperactivity Disorder (ADHD) [47]; The Barratts Impulsiveness Scale-11 (BIS-11) [48]; Depression, Anxiety, Stress Scale (DASS-21) [49]; Wellness Questionnaire - the Short Form-36 [50, 51]; plus customised questions on sleep.

The prisoners will also be asked at the end of the trial which treatment they thought they were on.

### Criteria for discontinuing or modifying allocated interventions {11b}

Any report of an adverse event provided by the on-site Project Officer will be evaluated by DG (clinical academic forensic psychiatrist with expertise in clinical research drug trials), and if significant, the participant will discontinue participation. Participants may also withdraw from the study at any time, and if desired consulted prisoner medical services of any medical needs.

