## Outcomes {12}

### Primary outcome measure

Aggressive behaviour will be assessed by the IBOS (Table 1) reported as a single measure, in addition to the number and severity of reprimands with both measures explained below.

**Table 1 Tab1:** Summary of the study outcome measures and methods

Variables	Methods	Who completes the task?
Primary outcome measure		
Aggressive behaviour	Converting routinely collected case notes into a numerical score of aggressive behaviour using the IBOS ([name], [name], [name]. The Inmate Behaviour Observation Scale (IBOS): A measure of prisoner aggression and violence based on inmate case notes, in preparation/forthcoming)	Correctional Officer on secondment as a Project Officer
Secondary outcome measures		
1. Aggressive behaviour	Counting the routinely collected reprimands into a numerical score and noting them as aggressive or non-aggressive	Correctional Officer on secondment as a Project Officer
2. Questionnaires		
Aggressive behaviour	Aggression Questionnaire [45]	Study participant with or without assistance from the Project Officer
Attention deficit disorder	Brown Attention Deficit Disorder Scales (BADDS, [46])	Study participant with or without assistance from the Project Officer
Attention deficit hyperactivity disorder	Conners’ Attention Deficit Hyperactivity Disorder (AHDH, [47])	Study participant with or without assistance from the Project Officer
Depression and anxiety	21-item Depression and Anxiety Stress Scale (DASS, [49])	Study participant with or without assistance from the Project Officer
Impulsivity	Barratt Impulsiveness Scale (BIS-Brief, [48])	Study participant with or without assistance from the Project Officer
Demographic questionnaire	In-house demographic questionnaire	Study participant with or without assistance from the Project Officer
Health questionnaire	SF-36 [50, 51] general health questionnaire, with additional questions on sleep	Study participant with or without assistance from the Project Officer
Secondary outcome measures		
3. Muscle strength	Dynamometer [52]	Correctional Officer on secondment as a Project Officer
Tertiary outcome measures		
1. Improved engagement in rehabilitation programmes	Completion of programmes and attrition of programmes	Manager of Offender Services & Programs (MOSP)/Manager Offender Development (MOD) will assist the Project Officer
2. Recidivism		CIG DG and Corrective Services Head Office
Other assessments		

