#### Inmate Behaviour Observation Scale (IBOS)

Actual instances of hostile and aggressive behaviour are routinely recorded as prisoner incident reports, where an officer considers the behaviour substantial enough to warrant sanction. However, the intensity of such behaviour required to warrant sanction fails to capture the range and diversity of hostile and aggressive behaviours and thus results in a low incidence rate. Further, different jurisdictions have developed different metrics for the classification of behavioural disorder. Thus, ([name], [name], [name]. The Inmate Behaviour Observation Scale (IBOS): A measure of prisoner aggression and violence based on inmate case notes, in preparation/forthcoming) developed a generic behavioural observation rating scale (IBOS) for use across jurisdictions. The IBOS is a 7-point scale which classifies prisoner behaviours across an 8-week period using data derived from individual prisoner case notes. Case notes are routinely recorded by custodial and non-custodial staff in the Offender Integrated Management System (OIMS) database to report and capture a majority of significant observations and interactions with prisoners. A score of − 1 is applied to all instances recorded in that week of *pro-social behaviour*, while a score of 0 is given if there were no behaviours of significance recorded. Thereafter, instances of hostile/aggressive behaviour are scored from 1 (non-compliant) to 5 (physically aggressive), with each level of hostility/aggression operationally defined and illustrated by examples. Thus, higher scores are associated with greater levels of aggressive behaviour. Inter-rater reliability of the IBOS was 0.844 for repeat raters ([name], [name], [name]. The Inmate Behaviour Observation Scale (IBOS): A measure of prisoner aggression and violence based on inmate case notes, in preparation/forthcoming). The IBOS is a validated tool that can be used across jurisdictions. The IBOS is significantly correlated with institutional records of misconduct or reprimands ([name], [name], [name]. The Inmate Behaviour Observation Scale (IBOS): A measure of prisoner aggression and violence based on inmate case notes, in preparation/forthcoming) which are the most common measure of aggression in prison studies. The IBOS has been found to significantly correlate with both the Aggression Questionnaire (AQ) and the Brown’s Attention Deficit Disorder Scales (BADDS) [7], and given that the AQ and the BADDS are also significantly correlated [53], this adds to its construct validity.

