
#### Number and severity of reprimands

If an act of aggressive behaviour warrants a reprimand, they are recorded in the OIMS database by Correctional Officers. The reprimands will be extracted from the OIMS system by the Project Officer and classified as violent or non-violent cases.

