### Sample size {14}

Our study is a randomised controlled trial powered to show a difference between treatment and placebo control of 25% in the proportion of participants experiencing a reduction in aggressive behaviour as measured by a change in the IBOS. Given the nature of the prison populations, it is likely that there will be an effect of prison in the analysis, and therefore, a design effect accounting for the intra-cluster correlation is incorporated in the sample size estimation with a conservatively estimated ICC of 0.03. Based on our pilot data, we anticipate that attrition will likely be high (~ 40%) with the sample size for recruitment appropriately inflated to account for this. Overall, a total sample size of 600 with 360 completing the study enables a difference of 25% to be detected with 80% power and an alpha level of 0.05.

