## Statistical methods

### Statistical methods for primary and secondary outcomes {20a}

In the simplest case, this study is designed to determine the difference between groups as proportion of responders to the treatment allocation. This analysis will be performed using a generalised linear mixed model adjusted for clustering by prison. IBOS scores will also be analysed using a form of generalised linear mixed model or generalised additive mixed models depending on the final distribution of the IBOS scores. These models also allow for the correlated nature of repeated measures over time and the correlation between prisoners from the same institution. Secondary measures will be analysed using linear mixed, or generalised linear mixed models again depending on the distributional form of the variable. These analyses will be conducted using STATA or R.

The data will also be analysed according to the change in the omega-3 index [24] as recommended by ISSFAL [24].

Our policy implementation is based on the primary outcome measure, the IBOS. The secondary outcome measures are hypothesis generating.

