### Methods in analysis to handle protocol non-adherence and any statistical methods to handle missing data {20c}

The primary analysis with be on an intention-to-treat basis. A per-protocol analysis will be performed on the subgroup deemed to be compliant with the trial protocol. Longitudinal analyses will be performed using restricted maximum likelihood, and therefore, all participants providing partial data will be included in the analysis.

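### The adverse-event rule ends participation without separating stopping capsules from leaving the study, so IBOS and reprimand data still obtainable from routine records may be given up

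*Protocol article*

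**What the plan says.** Section 11b of the protocol article, whose heading concerns discontinuing or modifying the allocated interventions, gives one rule for a significant adverse event: "if significant, the participant will discontinue participation". The next sentence begins "Participants may also withdraw from the study at any time". The article does not say whether outcome data are still collected once a man stops his capsules.

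The outcomes do not depend on capsule-taking. Table 1 describes the primary outcome as "Converting routinely collected case notes into a numerical score of aggressive behaviour using the IBOS". The IBOS section adds that "Case notes are routinely recorded by custodial and non-custodial staff in the Offender Integrated Management System (OIMS) database". For reprimands, "The reprimands will be extracted from the OIMS system by the Project Officer".

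On analysis, section 20a describes the simplest comparison as the "difference between groups as proportion of responders to the treatment allocation", and section 14 defines response through a change in the IBOS. Section 20c states: "The primary analysis with be on an intention-to-treat basis". It adds that longitudinal models fitted by restricted maximum likelihood will include men with partial data.

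**The concern.** A rule for adverse events should say two things: what happens to the treatment, and what happens to follow-up. Section 11b uses one phrase for both. If Project Officers take it at its word, a man with a significant event leaves the trial and nobody scores his later case notes.

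That loss would be avoidable. Men due for release within 16 weeks are excluded, so most men who stop early should still be in custody and generating case notes. The loss would also be of the kind that intention-to-treat analysis is meant to prevent. Removal for adverse events can differ by arm, so the missing responder outcomes need not be missing at random. If omega-3 caused more removals, and the removed men would have responded less often than those who stayed, the responder difference would be overstated. An excess of such removals on placebo would push it the other way.

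**Working it through.** **The text, side by side**

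1. The heading of 11b refers to interventions, which permits a capsules-only reading. The rule itself refers to participation. The following sentence, with its *also*, sets leaving the study alongside the rule. The plain reading is that the man leaves the trial, but the wording does not settle it.
2. Table 1 and the IBOS and reprimand sections show that both outcomes come from records kept routinely in the prison database. No visit, questionnaire or capsule is needed to obtain them.
3. Responder status (sections 14 and 20a) needs a change in IBOS, and so a score after baseline. Including partial data (20c) helps the longitudinal score models. It does not create a responder status for a man with no follow-up score.

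**The plan's own figures**

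Section 14 gives 600 recruited, about 40% attrition and 360 completing: 600 × (1 − 0.40) = 360, which agrees. With 1:1 allocation that is 300 recruited and 180 with data per arm. The planned difference of 25% is read here as 25 percentage points.

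**Size of the possible bias**

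The article gives neither an adverse-event rate nor a placebo response, so the following are assumptions.

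- k = excess omega-3 men removed under the rule: 3, 6 or 15 of 300 (1%, 2% or 5%).
- p1 = omega-3 response among the 180 men with data.
- q = response the removed men would have shown.

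The rate with the removed men kept is (180 × p1 + k × q)/(180 + k). Subtracting it from p1 gives the overstatement:

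k × (p1 − q)/(180 + k)

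*Removed men respond like placebo men, so p1 − q = 0.25:*

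- k = 3: 0.75/183 = 0.0041, or 0.4 points
- k = 6: 1.5/186 = 0.0081, or 0.8 points
- k = 15: 3.75/195 = 0.0192, or 1.9 points

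*None of the removed men would have responded (q = 0), with placebo response 30% to 50%, so p1 = 0.55 to 0.75:*

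- k = 3: 1.65/183 to 2.25/183, or 0.9 to 1.2 points
- k = 6: 3.3/186 to 4.5/186, or 1.8 to 2.4 points
- k = 15: 8.25/195 to 11.25/195, or 4.2 to 5.8 points

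The bias passes about 2.5 points only when removals reach several per cent of one arm and the removed men would have responded much less often than placebo men.

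**The case against.** The other side has real points.

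- **The capsules-only reading is available.** The heading supports it, and the second sentence can be read as a contrast: stop the intervention after an event and, separately, leave the study if you wish. A reader might infer that the plan orders case-note scoring to stop. It does not say so, and the intention-to-treat statement points the other way. This stands, and it limits the finding to wording that permits the loss.
- **The article is a condensed account.** A full protocol and a procedures manual exist and are not shown, and they may cover follow-up after stopping. This stands for any missing detail. It does not excuse the one rule the article does state, which is phrased in terms of participation.
- **What an early stopper contributes cannot be seen.** The schedule in Table 2 is not shown, and section 20a also plans repeated-measures models of IBOS scores. Such a man may contribute something to those models. The responder comparison still needs a follow-up score.
- **Few events are expected.** Section 30 expects no harms, and section 22 expects at most minor events such as bruising after blood collection, which is not specific to either arm. This stands and keeps the size small.

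Two stronger readings are tempting. First, a reader might connect this rule with the 40% attrition. Section 14 takes that figure from pilot data and does not attribute it to adverse events. Second, a reader might infer that section 17b forbids revealing a man's allocation and so conflicts with 11b. Section 17b is a forecast that unblinding will not be needed. Stopping capsules requires no knowledge of which oil a man took. An independent third party manages the list (17a), a person independent of the study holds the key, and jars carry participant identifiers (16b). A query about one man could therefore be answered. What is absent is a written procedure, which an article may leave to the full protocol. Nothing suggests that the whole list would be decoded.

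**Conclusion.** The point holds as a minor, inexpensive improvement. Section 11b does not distinguish stopping capsules from leaving the study. On its plain wording it gives up outcome data that the trial could still collect and that its intention-to-treat analysis needs.

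From adverse events alone the expected effect is under about 1 point of the planned 25, for 1% to 2% excess removals in the omega-3 arm with placebo-like response. The upper figure of 5.8 points needs 15 extra removals in that arm, no response in any of those men, and a 50% placebo response. All of these rest on assumed removal and response rates, and the direction would reverse if the excess were on placebo.

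The same distinction would matter more for men who stop capsules for other reasons while still in custody, since total attrition is expected to be far larger than adverse-event removals. How many such men there would be cannot be read from the article.

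**What to change.** Reword section 11b to state that:

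1. after a significant adverse event the capsules stop;
2. extraction of IBOS and reprimands from the prison database continues to the planned end of follow-up, unless the man withdraws consent for use of his data;
3. he is analysed in his allocated arm;
4. the same applies to any man who stops capsules for any reason while still in custody.

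The cost is a short ethics amendment during recruitment, which began in April 2019, and an instruction to Project Officers. No new staff, visits or assessments are needed, only scoring of case notes that are kept anyway. The consent form is not shown, so the sponsor should check that existing consent covers case-note extraction after capsules stop. If it does not, the change can apply only to men who give that consent.
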